### Relevant concomitant care permitted or prohibited during the trial {11d}

The hospital staff and enrolled patients are permitted to engage in any and all routine necessary concomitant medical treatments. We do not define any prohibitions.

### Provisions for post-trial care {30}

The trial does not have any formal procedures for post-trial care.

### Outcomes {12}

#### Primary outcome

##### Physician level

The primary outcome measure for the ED-level implementation strategy is DHT or CRM performance documentation (timing: during initial ED visit only).

##### Patient level

The primary outcome measure for the patient-level intervention is the dizziness handicap inventory (DHI) patient reported outcome (PRO) and will be obtained at weekly intervals for 1 month.

#### Secondary, exploratory, safety outcomes, and adverse events

##### Physician level

Secondary healthcare utilization related outcomes include the following:Brain imaging (head CT, brain MRI)Hospital admissionLength of stay in the ED

Safety outcomes include the following:Stroke hospitalizations within 30 days of ED/hospitalizationReturn visits to ED/urgent care/hospitalization for dizziness within 30 days

Adverse events related to the use of DHT/CRM (see Section 11)

##### Patient level

Secondary and exploratory outcomes include the following:Days-Out-Of-Role
Patient Global Impression of ChangeWorld Health Organization Well Being IndexPatient Health Questionnaire (PHQ)−4DHT/CRM use
Gaze-stabilization useSatisfaction with the materials

##### Safety outcomes

Stroke hospitalizations within 30 days of ED/hospitalizationReturn visits to the ED/urgent care/unscheduled hospitalization for dizziness within 30 days

Adverse events within 30 days related to the use of DHT/CRM, gaze stabilization exercises, walking exercises

### Participant timeline {13}

Figure 2 depicts an overview of the timeline of ED (specific aim 1) and participant level (specific aim 2) interventions.

**Fig. 2 Fig2:**
[figure not shown]
An overview of the timeline of ED (specific aim 1) and participant level (specific aim 2) interventions

### Sample size {14}

#### ED level

The Kaiser Permanente Southern California study site is comprised of 14 ED facilities, which collectively had nearly 40,000 dizziness visits in 2017. We plan to collect data on these visits for approximately 24 months. Thus, for the ED-level strategy, we will evaluate documentation of the DHT and CRM in >80,000 dizziness visits anticipating an increase in volumes over time. We hypothesize that the proportion of target visits with DHT/CRM documentation will increase from 7% in the pre-intervention period to 17% in the post-intervention period based on the findings in our estimated target population in DIZZTINCT-1. Even small absolute increases in the frequency of use of the DHT/CRM in the target population are considered clinically meaningful because the DHT and CRM are simple from a resource standpoint, not expensive, low risk and highly effective in clinical trials. With a sample of 80,000 visits, our power to detect an increase in DHT/CRM use from 7% in the control visits vs 17% in the intervention visits will be effectively 100% based on a two-sided test for independent proportions considering clustering at 14 sites, an intraclass correlation coefficient (ICC) by provider of 22% for provider-level variability (from DIZZTINCT-1) and a significance level of 5% (Table 1). We will use a mixed effects model to account for secular trends, hospital- and provider-specific features, and the potential relative association of the various components with the outcome. We estimate that 20% of the annual sample is the target population (80,000 × 0.20 = 16,000 visits) based on best available evidence that showed about 20% of dizziness patients in a national sample have BPPV characteristics. Of the 16,000 visits, approximately 8000 will be pre-intervention visits and 8000 post-intervention visits. With these volumes, we expect 560 (8000 × 7%) visits with DHT/CRM documentation in the pre-intervention period and 1360 (8000 × 17%) in the post-intervention period. Thus, we anticipate at least 1900 visits with DHT/CRM documentation. For modeling purposes, we should be able to easily meet and exceed the general rule of having 10 outcomes for each independent variable to avoid over-fitting. The large number of visits and anticipated outcomes will allow us to more closely examine differences at hospitals and provider types, and the relative influence of the various intervention components. We will be able to monitor use of the CME session, website, app, and reminder system and incorporate these variables in the model specific to the provider. The additional power will allow us to examine differences at hospitals and provider types, and the relative influence of the various ED-level implementation strategies.

**Table 1 Tab1:** Power calculations for ED-level stepped wedge design

Control, proportion outcome*	Intervention, proportion outcome*	Alpha	ICC**	Power for 80,000 visits	Minimum sample size for power >0.8
7%	17%	0.05	22%	0.999	468
7%	12%	0.05	22%	0.999	2028
7%	9.5%	0.05	22%	0.999	7800

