#### Supporting data

The scientific premise of DIZZTINCT-2 is based on prior work in DIZZTINCT-1 which defined the problems, created an implementation strategy and materials, and demonstrated that providers adopted the strategy [29]. DIZZTINCT-1 aimed to increase the use of DHT and CRM and promote a BPPV-centric approach to dizziness. The strategy was guided by the Consolidated Framework for Implementation Research (CFIR) and informed by ED provider interviews to identify barriers and facilitators to DHT and CRM use [9, 30].

The DIZZTINCT-1 stepped-wedge RCT found that the implementation strategy increased DHT or CRM use (odds ratio 2.44; 95% CI 1.42 to 4.20; *n* = 7635 visits) [29]. The DHT or CRM use increased from 7% in pre-intervention visits to 17% in post-intervention visits in the estimated target population with a high probability of BPPV diagnosis (1.5 to 3.5% among all dizziness visits) [29]. The strategy was safe, reducing head CT use (from 44 to 37%) and showing a trend toward lower hospital admission. No serious adverse events were related to DHT or CRM, and non-serious adverse events (nausea, vomiting, headache) were uncommon (<5% of visits) and resolved or improved. There was also a trend toward a lower rate of subsequent strokes after ED visits in intervention visits compared with control visits [29]. Qualitative analysis of provider interviews revealed that providers often had positive experiences using the materials and performing the DHT and CRM [29].

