#### Objective 1 (ED-level)

To determine the impact of an enhanced BPPV-centric implementation strategy on DHT/CRM performance in dizziness visits, at academic and nonacademic EDs, using a randomized stepped-wedge design. The strategy targets physicians and includes enhanced provider materials, patient-oriented resources, local champions, an online educational session, and reminder system.

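### The ED-level power statement and Table 1 pair DHT/CRM rates for target visits with the count of all dizziness visits, and the table matches neither the test described nor the 15-ED, 11-wave design

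*Protocol article*

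**What the plan says.** All references are to the protocol article.

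- **Hypothesis** (Sample size, ED level): "We hypothesize that the proportion of target visits with DHT/CRM documentation will increase from 7% in the pre-intervention period to 17"%. The rates belong to target visits.
- **Size of the target population** (same section): "We estimate that 20% of the annual sample is the target population (80,000 × 0.20 = 16,000 visits"). It continues: "Of the 16,000 visits, approximately 8000 will be pre-intervention visits and 8000 post-intervention visits". The expected event counts, 560 and 1,360, are computed from these.
- **Power statement** (same section): "With a sample of 80,000 visits, our power to detect an increase in DHT/CRM use from 7% in the control visits vs 17"%, put at effectively 100%, "based on a two-sided test for independent proportions considering clustering at 14 sites", with a provider ICC of 22%.
- **Table 1**, titled "Power calculations for ED-level stepped wedge design": for 7% versus 17%, 12% and 9.5% it gives power 0.999 at 80,000 visits in every row, and minimum sizes of 468, 2,028 and 7,800 for power above 0.8.
- **Earlier trial** (Supporting data): the rise from 7% to 17% was seen "in the estimated target population with a high probability of BPPV diagnosis (1.5 to 3.5% among all dizziness visits").
- **Objective 1**: the effect on "DHT/CRM performance in dizziness visits, at academic and nonacademic EDs", with no restriction to target visits. The physician-level primary outcome names no denominator.
- **Number of EDs**: 14 in the ED-level sample size section; 15 in 11 waves under Trial design; 12 in the text introducing Table 3, whose own footnote says 15.

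**The concern.** The power calculation takes its rates from one population and its sample size from another, five times as large. A reader cannot tell whether the ED-level primary analysis covers 16,000 target visits or 80,000 dizziness visits, or which of these Table 1 counts. The test described in the text is also not the stepped-wedge calculation that the table's title announces, and three ED counts are in play.

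The smallest-effect row is where this matters. The section calls even small absolute increases clinically meaningful, and relies on surplus power for analyses by hospital, provider type and intervention component. A flat 0.999 in all three rows supports those claims more strongly than a matched calculation would.

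**Working it through.** **1. Inputs.** Two-sided alpha 0.05; rates 7% versus 17%, 12% and 9.5%; ICC 22%; 80,000 visits; target share 20% (all from Sample size, ED level, and Table 1). All-visit rates 1.5% and 3.5% (Supporting data). ED-facility ICC 1.9% (Sample size, Patient level).

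**2. The test described does not give Table 1.** A plain two-proportion test needs 330, 1,078 and 3,800 visits in total (pooled variance), not 468, 2,028 and 7,800.

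**3. A stepped-wedge calculation does.** The three sizes share the divisor 156 = 12 × 13, and none is divisible by 14. Take the Hussey-Hughes variance with I EDs, T periods and n visits per cell:

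Var = I·s²(s² + Tτ²) / [(IU − W)s² + (U² + ITU − TW − IV)τ²]

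Here s² = (1 − ICC)·v/n, τ² = ICC·v, v = p₁(1 − p₁), and power = Φ(|p₂ − p₁|/SE − 1.96). U, W and V are, for the 0/1 treatment matrix, its total, the sum of squared period totals and the sum of squared ED totals. For 12 EDs, one crossing per step after one baseline period, U = 78 and W = V = 650. Then IU − W = 286 and U² + ITU − TW − IV = 6,084 + 12,168 − 8,450 − 7,800 = 2,002. With v = 0.07 × 0.93 = 0.0651 and ICC 0.22:

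| Row | n per cell | SE | Power | 156 × n | Power with n − 1 |
|---|---|---|---|---|---|
| 7% vs 17% | 3 | 0.0351 | 0.813 | 468 | 0.656 |
| 7% vs 12% | 13 | 0.0173 | 0.824 | 2,028 | 0.794 |
| 7% vs 9.5% | 50 | 0.00888 | 0.804 | 7,800 | 0.796 |

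All three printed sizes are matched exactly, and power at 80,000 exceeds 0.999 in each row, as printed.

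**4. All-visit rates.** If only target visits contribute, the rates are 0.20 × 7% = 1.4% against 0.20 × 17% = 3.4%, 0.20 × 12% = 2.4% and 0.20 × 9.5% = 1.9%. The first two agree with the article's 1.5% and 3.5%.

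**5. Same method, matched population.**

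| Row | Minimum size as printed | Minimum, all dizziness visits | Power, 16,000 target visits | Power, 80,000 visits at diluted rates |
|---|---|---|---|---|
| 7% vs 17% (1.4% vs 3.4%) | 468 | 2,652 | >0.999 | >0.999 |
| 7% vs 12% (1.4% vs 2.4%) | 2,028 | 10,296 | >0.999 | >0.999 |
| 7% vs 9.5% (1.4% vs 1.9%) | 7,800 | 41,184 | 0.981 | 0.974 |

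The ratios of the minimum sizes are 5.7, 5.1 and 5.3. With 1.5% versus 3.5% the minimum is 2,808 and power at 80,000 exceeds 0.999. For the last row, 16,000/156 = 102.6 visits per cell gives SE 0.00620, and 0.025/0.00620 − 1.96 = 2.07, so power is 0.981. On the all-visit scale v = 0.014 × 0.986 = 0.0138 and 80,000/156 = 512.8 per cell; SE is 0.00128 and 0.005/0.00128 − 1.96 = 1.95, so power is 0.974.

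**6. Layout closer to the stated design.** Assume 15 EDs in 11 waves with four pairs (placed in the first four waves) and 23 monthly periods (6 + 11 + 6). Power for the smallest-effect row:

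| Cluster ICC | Variance | 16,000 target visits | 80,000 visits |
|---|---|---|---|
| 22% | control rate | 0.93 | 0.91 |
| 22% | mean of both arms | 0.89 | 0.86 |
| 1.9% | control rate | 0.87 | 0.84 |
| 1.9% | mean of both arms | 0.81 | 0.78 |

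The other two rows stay at 0.999 or above throughout. Placing the pairs in other waves moves these figures by a few hundredths.

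**The case against.** The strongest defence is that little of substance changes. The hypothesised effect keeps power above 0.999 on either scale. The event counts and the 10-outcomes-per-variable argument already use 16,000. Read as target visits, 468, 2,028 and 7,800 are right under the table's own method and well below 16,000. Visits accrue from records whatever the table says. All of this stands, and it makes the point one of reporting and calculation, not of design.

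The 12-ED, 13-period layout is inferred: the article nowhere states it for Table 1. Table 1's asterisks also have no footnote in the text available, so a note may define the population or the ICC level. That lowers certainty about how the ICC was meant. It does not remove the mismatch, because the sentence in the text makes the same pairing.

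Three stronger readings are tempting and not supported:

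- **That power is wrong five-fold.** Only the minimum sizes change by that factor, only if read as dizziness visits, and because of the 20% share. The ED count is not the cause: 14 or 15 EDs in the same method move the two larger sizes by under 7%.
- **That small-effect power falls to about one half.** This needs a decay in within-ED correlation over time (such as a cluster autocorrelation of 0.8) for which the article gives no figure.
- **That the primary analysis must be on all visits.** Objective 1 points that way, the hypothesis points to target visits, and the outcome definition names no denominator.

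**Conclusion.** The point holds as an internal inconsistency. Target-visit rates are paired with the all-visit denominator, and Table 1 matches neither the 14-site test described nor the 15-ED, 11-wave design. Ample power for the hypothesised effect is not in doubt.

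What fails is the flat 0.999 in the 7% to 9.5% row, and the minimum sizes if they are taken as dizziness visits. The row's power is about 0.97 to 0.98 on the reconstructed layout and about 0.78 to 0.93 on the 15-ED layout, below 0.80 only in the least favourable combination. These figures rest on the reconstructed method, on the assumption that DHT/CRM documentation arises only in target visits and, for the wider range, on the assumed pairing and monthly calendar. The 22% is a provider-level ICC acting as the ED-level one, and the article's own ED figure is 1.9%.

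**What to change.** 1. State one analysis population for the ED-level primary outcome, consistently in Objective 1, the outcome definition and the sample size section.
2. Match rates to denominator. Either 16,000 target visits at 7% to 17%, or 80,000 dizziness visits at 1.5% to 3.5%, is acceptable. Label Table 1's visit counts accordingly.
3. Recompute Table 1 for the actual 15 EDs, 11 waves and calendar, with ED and provider ICCs as separate levels.
4. Reconcile the 12, 14 and 15 EDs, and describe the stepped-wedge calculation actually used in place of the independent-proportions test.

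The cost is recalculation and wording, with no change to design or data collection. The smallest-effect row becomes somewhat less favourable, and the remarks on surplus power should be worded to match.

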### Strategies to improve adherence to interventions {11c}

We plan to assess implementation fidelity in order to monitor adherence during the trial and in plans to give recommendations for implementation in other settings. Our fidelity assessments have both quantitative and qualitative components to capture clinical and strategy fidelity. The quantitative data is the use of the educational session, print materials, website, app, checklist, and electronic medical record reminders. The use data will directly inform the interpretation of necessary components. Qualitative data will be obtained from semi-structured interviews with key stakeholders. We will sample individuals to capture a range of experiences with the materials and strategy (e.g., high frequency resources users, low frequency resource users, local clinical leaders). We will use an interview guide developed with our multidisciplinary team to assess training uptake, adherence to content, quality of use in practice, barriers to use in practice, resource dosage, satisfaction, and site adaptations. Interviews with local champions will specifically seek to capture variability in the approaches to provider notifications. Regarding, participant (patient-level) follow up—we use a variety of communication methods (email, phone, text) and financial incentives to promote adherence to the data collection.

SPIRIT guidance: Strategies to improve adherence to intervention protocols, and any procedures for monitoring adherence (e.g., drug tablet return, laboratory tests).

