## Assignment of interventions: allocation

### Sequence generation {16a}

#### ED level

The overall study period will be approximately 24 months. After the 6-month pre-intervention period, the sites will receive the intervention in 11 waves. The order will be determined by using a random number generator. The intervention start date at each ED is the date the physicians are auto enrolled for the online CME and the printed education materials (i.e., posters, notecards) are distributed on site.

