### Methods in analysis to handle protocol non-adherence and any statistical methods to handle missing data {20c}

Many participants will not complete all 4 surveys; however, the longitudinal models planned for the primary analyses above should account for this. When appropriate, multiple imputation will be used. Exploratory analyses may focus on how many physicians at a site used the CME intervention and if possible, we will conduct analyses evaluating the primary outcome within the subset of physicians who viewed the CME.

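### The ED-level DHT/CRM model can be read as placing provider uptake beside the intervention indicator, whose coefficient would then be a contrast among non-users and not the randomised effect

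*Protocol article*

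**What the plan says.** All places are in the protocol article.

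- **Outcome and question.** Outcomes {12}, Physician level: "The primary outcome measure for the ED-level implementation strategy is DHT or CRM performance documentation". Objectives {7}, Objective 1, asks for the impact of the implementation strategy on DHT/CRM performance under a randomised stepped-wedge design.
- **Model.** Sample size {14}, ED level, has the only description for this outcome: "We will use a mixed effects model to account for secular trends, hospital- and provider-specific features, and the potential relative association of the various components". Later in that section the authors describe a further capability: "monitor use of the CME session, website, app, and reminder system and incorporate these variables in the model specific to the provider".
- **Timing of the components.** Sequence generation {16a}: "The intervention start date at each ED is the date the physicians are auto enrolled for the online CME"; the same sentence adds the distribution of the printed materials. Who will be blinded {17a} says that sites do not get the educational materials before their time point.
- **Status of the use data.** Strategies to improve adherence {11c} treats component use as fidelity data: "The quantitative data is the use of the educational session, print materials, website, app, checklist, and electronic medical record reminders".
- **Related exploratory work.** Section {20c}: "Exploratory analyses may focus on how many physicians at a site used the CME intervention", and, if possible, analyses "evaluating the primary outcome within the subset of physicians who viewed the CME".
- **What is written out elsewhere.** Statistical methods {20a} gives a full covariate list for the DHI model only. That model has a 0/1 ED-level indicator and no uptake variables.

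**The concern.** Use of the study's CME, website, app and reminders cannot occur before the ED's randomised start date, and the strategy is meant to work partly through that use. These variables are therefore consequences of the intervention. A model that holds them beside the intervention indicator splits the effect into a part carried by uptake and a remainder, and the intervention coefficient reports only the remainder.

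Uptake is also not randomised. CME enrolment is automatic, but viewing the session is voluntary, and the account of the predecessor trial's limitations reports low provider participation at non-academic facilities. Providers who use the materials may differ from those who do not in how readily they would perform a DHT anyway.

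At stake is the answer to Objective 1. The near-certain power gives no protection, because the issue is which quantity is estimated and not how precisely. The choice also should not stay open: {17a} says the data analysts are not blinded, and Trial status reports that the last participant was enrolled in March 2025.

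**Working it through.** **1. The plan's own figures.** Sample size {14} expects that "the proportion of target visits with DHT/CRM documentation will increase from 7% in the pre-intervention period to 17% in the post-intervention period".
- Expected events: 8000 × 7% = 560 and 8000 × 17% = 1360, total 1920. This matches the stated minimum of 1900.
- Power for 7% against 17% with 80,000 visits, two-sided 5%, provider ICC 22%: dividing the sample by 1 + (m − 1) × 0.22 gives about 1.000 for m = 1 to 100 visits per provider. This agrees with the 0.999 in Table 1. The value of m is not stated, so the range is an assumption.

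Neither figure depends on the point raised here.

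**2. Total effect.** Odds ratio = (0.17/0.83) / (0.07/0.93) = 0.2048 / 0.0753 = 2.72, log odds ratio 1.00. The risk difference is 10 points.

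**3. The coefficient once uptake is in the model.** Let X be the intervention indicator and U = 1 for a provider who used a component. U can be 1 only when X = 1. In logit(p) = a + bX + cU, leaving secular trend aside, a post-intervention non-user has X = 1 and U = 0, so

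exp(b) = odds(non-user rate after the step) / odds(7%).

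Let u be the share of post-intervention target visits seen by users. The average is held at 17% by u × (user rate) + (1 − u) × (non-user rate) = 17%. The share u does not enter exp(b). Neither u nor the non-user rate is in the article, so both are assumed.

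| Non-user rate | User rate, u = 0.3 | u = 0.5 | u = 0.9 | Risk difference in b | exp(b) |
|---|---|---|---|---|---|
| 7% | 40.3% | 27.0% | 18.1% | 0 points | 1.00 |
| 9% | 35.7% | 25.0% | 17.9% | 2 points | (0.09/0.91)/(0.07/0.93) = 1.31 |
| 12% | 28.7% | 22.0% | 17.6% | 5 points | (0.12/0.88)/(0.07/0.93) = 1.81 |

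**4. Simulation with secular terms.** Assumed layout: 14 sites, 11 waves, 24 months, 25 providers per site and 2 visits per provider-month (14 × 25 × 24 × 2 = 16,800 visits), latent provider ICC 0.22, and 20 repetitions per scenario. Logistic models had fixed site and month effects. The self-selected scenarios set a correlation of 0.5 between a provider's motivation to take up the materials and baseline tendency to perform DHT/CRM.

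| Uptake | Direct log OR | Self-selection | Step log OR, no uptake term | Step log OR, uptake term |
|---|---|---|---|---|
| 50% | 0 | none | 1.168 | −0.013 |
| 50% | 0.4 | none | 1.106 | 0.368 |
| 70% | 0 | none | 1.129 | −0.078 |
| 70% | 0.4 | none | 1.062 | 0.365 |
| 50% | 0 | 0.5 | 1.344 | −0.393 |
| 50% | 0.4 | 0.5 | 1.216 | −0.116 |
| 70% | 0 | 0.5 | 1.239 | −0.623 |
| 70% | 0.4 | 0.5 | 1.132 | −0.247 |

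Without self-selection, the coefficient drops to roughly the direct effect. With self-selection it turns negative: exp(−0.116) = 0.89 to exp(−0.623) = 0.54, although the strategy works in every scenario. The fitted models had no provider effect. A provider random effect, which the plan's wording suggests, would be expected to absorb part of the self-selection, so these negative values show that the sign can change and do not estimate by how much.

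**The case against.** The strongest reply is that the article never makes the uptake-adjusted coefficient the primary result. The model sentence sits in a sample-size section and names no intervention indicator, covariate set or primary contrast. The contrast used for power, the wording of Objective 1 and the predecessor's reported odds ratio are all total effects. The sentence on uptake says only what the authors will be able to do, and it stands among remarks on what the spare power allows. The DHI model, the one model written out, has a clean 0/1 indicator. An SAP not shown may separate the analyses.

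Much of this stands, and it limits the point to wording that can be read in a harmful way. It does not remove it. The first model sentence already joins secular trends and the components in one model, the later sentence refers back to the model, and nothing in the article states an ED-level model free of uptake. That is a loose specification on the page, not merely detail left to the SAP.

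Two further replies also stand:
- Not every component is chosen by the provider. Reminders are a system element and CME enrolment is automatic, so uptake is only partly self-selected.
- The CME-viewer analysis is already called exploratory in {20c}.

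**Conclusion.** The point holds as an ambiguity that should be closed. Followed literally, the ED-level text would condition the intervention effect on uptake that follows crossover, and the coefficient would no longer answer Objective 1. Against a total odds ratio of 2.72, it would be 1.00, 1.31 or 1.81 for non-user rates of 7%, 9% or 12%. Those rates are assumptions, and the fall below 2.72 rests on the trial's own premise that using the materials raises DHT/CRM use.

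A reader might infer three stronger things that the documents do not support:
- **That the plan fixes the adjusted coefficient as its primary effect.** No section says so.
- **That the trial would show no effect although the strategy worked.** An odds ratio of 1.00 needs the whole effect to pass through the four measured components. Intervention description {11a} also lists local champions, posters, notecards and dot phrases, which can act without them.
- **That the bias always stops at or before zero.** If keener providers take up more, the coefficient can fall below an odds ratio of 1.

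No stated power or sample size changes.

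**What to change.** State the primary ED-level DHT/CRM model as: the intervention indicator, calendar period, pre-intervention hospital and provider characteristics, and random ED and provider effects, with no uptake variables. Say that its intervention coefficient is the answer to Objective 1.

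Put use of the CME, website, app and reminders in a separate exploratory model labelled non-randomised. The CME-viewer subset in {20c} needs at most the same label.

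The cost is a few sentences in the analysis plan, or confirmation that the plan already says this. No data collection changes and no planned component analysis is lost. Settle it before the ED-level results are examined, if that is still possible.
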